### Statistical analysis

Data will be de-identified, encoded, and stored in the database using the Excel Program. The software SPSS 22.0 will be used for the analysis of data. The description of quantitative variables will be expressed in mean, standard deviation, minimum value, median and maximum value. Qualitative variables will be described in absolute and relative values (%). A 95% confidence interval and 0.05 significance will be considered for all tests. Both per-protocol and intention-to-treat analyses will be performed.

A linear mixed-effect model will be used to analyze the ICIQ-SF score. In the reassessment, individuals’ values will be considered random effects, and the groups, the times, and the interaction between them will be regarded as fixed effects. In addition, the McNemar test will verify changes in categories variables before and after the intervention. Both per-protocol analysis [11–13] and an intention-to-treat analysis will be also conducted.

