**Methods:**

This is a protocol for a randomized controlled trial that will include obese women reporting UI and being able to contract their pelvic floor muscles. The participants will be randomly allocated in two groups: group 1 will participate in a 12-week protocol of low-calorie diet delivered by a multi-professional team at a tertiary hospital; group II will receive the same low-calorie diet protocol during 12 weeks and will additionally participate in 6 group sessions of supervised PFMT delivered by a physiotherapist. The primary outcome of the study is self-reported UI, and severity and impact of UI on women’s quality of life will be assessed by the ICIQ-SF score. The secondary outcomes will be adherence to the protocols assessed using a home diary, pelvic floor muscle function assessed by bidigital vaginal palpation and the modified Oxford grading scale, and women’s self-perception of their PFM contraction using a questionnaire. Satisfaction with treatments will be assessed using a visual analog scale. The statistical analysis will be performed by intention to treat and multivariate analysis of mixed effects will be used to compare outcomes. The complier average causal effects (CACE) method will be used to assess adherence. There is an urgent need for a high-quality RCT to investigate if the association of a low-calorie diet and PFMT can provide a larger effect in the improvement of urinary incontinence reports in women with obesity.

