### Sample size calculation

The sample calculation was estimated considering a significance level of 5%, power of 20%, and difference of 4 points on the final score of the primary outcome, ICIQ-SF, between groups at the end of treatment [10]. The value of 4 points is equivalent to the minimum value for change in the questionnaire score. Thus, the sample will be composed of 22 participants.

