### Intervention

Women randomized to Group 1 will receive counseling from the hospital staff. They will attend 3 meetings (once a month), where a multi-professional team from the bariatric surgery outpatient clinic will address different topics related to nutrition including advice on the quality of food, mindful eating, identification of signs of hunger and satiety, and emotional triggers that lead to emotional eating. In addition, each participant will undergo individual nutritional assistance to assess food consumption, anthropometric measures, and body composition and will receive more specific guidelines on nutrition and an individualized low-calorie diet and monitoring. Outpatient care will last 12 weeks and women in this group will not receive instructions and a supervised PFMT protocol, however for ethical reasons, after the data collection is finished women belonging to this group will be invited to receive six supervised sessions of PFMT and will receive the same booklet of exercises on PFMT delivered to group II.

The participants randomized to group II will also receive the same counseling related to nutrition and also an individualized low-calorie diet given by the hospital staff; additionally, they will participate in six face-to-face physiotherapy sessions supervised by a physiotherapist in groups of a maximum of 10 participants, for 12 weeks in interspersed weeks.

In the weeks when there is no face-to-face supervised session, the same physiotherapist will encourage home PFMT by phone, calling each participant of Group II only. An intensive PFMT will be encouraged by the physiotherapist. The PFMT protocol will consist of 4 sets of ten maximum perceived voluntary contractions sustained for 6 s with a 6-s resting period between the contractions. At the end of a series of 10 contractions, five rapid contractions of the PFM will be performed. Two minutes interval will be given between each set performed.

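### PFMT is delivered in shared training groups in group II only, but the ICIQ-SF model has a random effect for the woman alone; if outcomes correlate within training groups, its p-value and interval are too optimistic

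*Protocol article*

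**What the plan says.** The Intervention section has group II attend "six face-to-face physiotherapy sessions supervised by a physiotherapist in groups of a maximum of 10 participants, for 12 weeks in interspersed weeks". Between these sessions a physiotherapist telephones each group II woman, and she exercises at home. Group I gets the same dietary counselling but is offered supervised PFMT only once data collection is over.

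Allocation is from a computer-generated random list in sealed envelopes (Randomization and blinding process). Women are therefore randomised one by one, and grouping happens afterwards, in one arm.

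For the ICIQ-SF score, the Statistical analysis section names a linear mixed model in which "individuals’ values will be considered random effects, and the groups, the times, and the interaction between them will be regarded as fixed effects". It names no other random effect. The Sample size calculation targets a "difference of 4 points on the final score of the primary outcome, ICIQ-SF, between groups at the end of treatment" and ends: "Thus, the sample will be composed of 22 participants". It mentions no design effect or ICC.

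**The concern.** Individual randomisation with group delivery in one arm gives a partially nested design. Women in the same training group share session times, group dynamics and calendar period, and these can make their 12-week scores resemble each other. A random effect for the woman links her two visits; it does not link her to the others in her group.

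If that resemblance exists, the mean of group II varies more from trial to trial than the model assumes. The standard error of the group-by-time effect is then too small, the 5% test rejects too often, and the 95% interval covers less than 95%. The 22 women also carry less information about the 4-point difference than 22 independent women would.

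This is not a detail left open for an analysis plan, because the article itself states the random-effects structure.

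**Working it through.** **Inputs from the article.** Total sample 22; difference 4 points; significance level 5%; training groups of at most 10, in group II only; random effect for the individual only.

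**Assumptions.** Two-sided test; 11 women per arm (the allocation ratio is not stated); each woman stays in one training group; complete data; ICC 0.02 to 0.10 on the analysed score. With two visits and complete data, the group-by-time effect in a random-intercept model equals a two-sample comparison of change scores, so a two-sample t-test is a fair stand-in.

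**Step 1: the plan's own figure.** No standard deviation (SD) is given, so 22 can only be solved backwards. By the normal approximation, SD = 4 × √(11/2) / (1.960 + 0.842) = 9.381 / 2.802 = 3.35, if the printed power of 20% means a type II error of 20%. Read literally, it gives 9.381 / (1.960 − 0.842) = 8.39. The figure can be neither confirmed nor refuted. The false-positive rates below do not depend on the SD.

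**Step 2: variance inflation.** With training groups of size m, the design effect in group II is

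DE = 1 + (Σm²/Σm − 1) × ICC.

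With equal arms, the true standard error of the contrast is √((1 + DE)/2) times the one that assumes independence. For 6+5, Σm²/Σm = 61/11 = 5.545; for 10+1, 101/11 = 9.182; for 4+4+3, 41/11 = 3.727. For example, 10+1 at ICC 0.05 gives DE = 1 + 8.182 × 0.05 = 1.409 and √(2.409/2) = 1.098.

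**Step 3: false-positive rate.** Simulated trials of 11 v 11, with a training-group effect in group II only and a two-sided 5% t-test:

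| Split | ICC | DE | SE ratio | False positives |
|---|---|---|---|---|
| any | 0 | 1.000 | 1.000 | 5.0% |
| 6+5 | 0.02 | 1.091 | 1.022 | about 5.5% |
| 6+5 | 0.05 | 1.227 | 1.055 | about 6.3% |
| 6+5 | 0.10 | 1.455 | 1.108 | about 7.7% |
| 10+1 | 0.02 | 1.164 | 1.040 | about 5.9% |
| 10+1 | 0.05 | 1.409 | 1.098 | about 7.5% |
| 10+1 | 0.10 | 1.818 | 1.187 | about 10.0% |
| 4+4+3 | 0.05 | 1.136 | 1.034 | about 5.8% |

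**Step 4: power.** At SD 3.35 (80% power under independence), power with the correct standard error is Φ(2.802/SE ratio − 1.960). At ICC 0.05 and 0.10 this is about 76% and 72% for 6+5, and 72% and 66% for 10+1. These figures rest on the back-solved SD.

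**Step 5: can the trial estimate the clustering itself?** Hardly. Two training groups leave 1 degree of freedom for the between-group variance, where the critical t is 12.7, against 2.09 on 20 degrees of freedom. An approximate analysis that estimated this variance from groups of 6+5 had about 54% power at ICC 0.05.

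**The case against.** The strongest reply is that nothing in the article shows the ICC to be above zero, and some features point to a small one. Much of the training is at home, with individual telephone calls and diaries, and the text reads as if one physiotherapist leads all sessions, so therapist differences would not vary between training groups. At ICC 0.02 the excess is under one percentage point. This stands. A reader might infer that the stated interval is in fact too narrow; the documents support only the conditional statement.

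A reader might also infer that group II must contain at least two training groups, because 11 exceeds the cap of 10. That needs exactly 11 women. Under simple 1:1 randomisation of 22, group II has 10 or fewer with probability (1 − C(22,11)/2²²)/2 = 42%, so a single training group is possible. Nor does the article say that women keep the same group throughout.

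Third, one might want the primary analysis replaced by one with the ICC fixed at 0.05. That value has no source in the documents. If the true ICC is 0, such a test runs at about 4% (6+5) or 3.3% (10+1), and power falls from 80% to about 77% or 74%. If the true ICC is 0.10, it still runs at about 6% or 7%. This trade-off supports a sensitivity analysis, not a new primary analysis.

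Finally, the monthly diet meetings might also be held in groups. Both arms have them, so they do not create the one-arm clustering described here, but the article does not rule out clustering from that source.

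**Conclusion.** The point holds in conditional form. The stated model leaves out the training-group level, and any positive correlation within training groups makes its treatment p-value and interval too optimistic. With 11 women per arm and ICC 0.02 to 0.10, the nominal 5% test runs at about 5.5% to 7.7% for 6+5 and 5.9% to 10.0% for 10+1. The upper figure combines the largest ICC considered with the most uneven split. At ICC 0 there is no error.

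One limit remains whatever is done in the analysis. If group II forms a single training group, or one physiotherapist leads all sessions, that shared effect cannot be separated from treatment.

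The effect is moderate and uncertain, but the trial status section says recruitment has not started, so the information needed can still be collected at almost no cost.

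**What to change.** 1. Record the training group of each group II woman in the database, and any change of group.
2. Within the existing cap, form groups of near-equal size rather than one full group and a remainder. At ICC 0.05, 4+4+3 gives about 5.8% false positives against about 7.5% for 10+1.
3. Keep the stated mixed model as primary. Pre-specify a sensitivity analysis that multiplies the standard error of the treatment contrast by √((1 + DE)/2), with DE = 1 + (Σm²/Σm − 1) × ICC, at ICC 0.02, 0.05 and 0.10, using the actual group sizes. If the arms differ in size (n₁ in group I, n₂ in group II), the variances 1/n₁ and DE/n₂ give √((n₂ + n₁ × DE)/(n₁ + n₂)). Fixed values are needed because two or three training groups cannot estimate the variance.
4. State in the sample size section that 22 makes no allowance for this clustering, and in the analysis section that a single training group or a single physiotherapist would leave the shared effect inseparable from treatment.

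The cost is one data field, some attention to group sizes and a few sentences; no women, staff or visits are added. The sensitivity intervals are about 2% (6+5, ICC 0.02) to 19% (10+1, ICC 0.10) wider than the primary interval, and a borderline result may not survive them.

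### The ICIQ-SF mixed model makes no baseline adjustment, so with 22 women it gives up precision that the baseline score, already collected, could supply

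*Protocol article*

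**What the plan says.** Under Statistical analysis, the protocol article states that "A linear mixed-effect model will be used to analyze the ICIQ-SF score". Individuals enter as random effects, and "the groups, the times, and the interaction between them will be regarded as fixed effects". That section names no baseline ICIQ-SF covariate and no constraint that the two groups share a baseline mean. It does not say which contrast of the model is the treatment effect.

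Table 2 and the Data collection section give two assessments of the ICIQ-SF: baseline and 12 weeks.

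Under Sample size calculation, the trial is sized on a "difference of 4 points on the final score of the primary outcome, ICIQ-SF, between groups at the end of treatment", and "the sample will be composed of 22 participants". No SD, correlation, allocation ratio or dropout allowance is given.

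**The concern.** Randomisation makes the true baseline means of the two groups equal. A model with a free group effect still estimates a baseline difference from the data. With only two visits, the interaction then subtracts that estimated difference in full, noise included. The week-12 contrast from the same model goes the other way and ignores the baseline score altogether. A baseline-adjusted estimate lies between them and lets the data, through the correlation, set how much of the baseline difference to remove.

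This matters more in a small trial. With 11 per arm, the standard error of the baseline difference is √(2/11) = 0.43 SD. A chance imbalance of at least half an SD (0.5/0.43 ≈ 1.17 standard errors) therefore arises in about 24% of such trials.

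At stake are the width of the primary confidence interval and, if the interaction is the test and the correlation is low, power below what the trial was sized for. The interaction's power depends on a correlation that the final-score sizing does not involve.

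**Working it through.** **Inputs from the protocol article.** Total of 22 women; 4-point difference in final ICIQ-SF; 5% significance; two visits; fixed effects of group, time and their interaction.

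**Inputs assumed.**
- Allocation 1:1, so 11 per arm.
- Two-sided test.
- 80% power. The article prints power as 20%, read here as the type II error.
- No dropout, and the same SD at both visits.
- Correlation ρ between baseline and week 12 of 0.2 to 0.7.

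**Step 1: the plan's own figure.** Without an SD, 22 cannot be reproduced forwards, so I solved for the SD that gives it. With 11 per arm, 4 points, two-sided 5% and 80% power, the t-test gives SD = 3.18 (normal approximation 3.35). The standard error of a final-score difference is 3.18 × √(2/11) = 1.36, and 4/1.36 = 2.95 on 20 degrees of freedom gives 80% power, as it must.

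**Step 2: what the model estimates.** I relied on a random-intercept model with group, time and interaction, fitted to simulated complete two-visit data. The interaction coefficient equalled the raw difference in mean change (−5.253 for both in one data set). The week-12 group contrast equalled the raw difference in final means (−4.598 for both in that data set).

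**Step 3: variances**, each multiplied by (2/11) × SD²:
- final score only: 1
- interaction (difference in change): 2(1 − ρ)
- baseline-adjusted: 1 − ρ²

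The interaction's standard error is 1.358 × √(2(1 − ρ)): 1.72, 1.61, 1.36 and 1.05 at ρ = 0.2, 0.3, 0.5 and 0.7. Dividing 4 by these gives 2.33, 2.49, 2.95 and 3.80.

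**Step 4: power and interval width.** The ANCOVA figures are simulated and include the cost of estimating the slope with 22 women.

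| ρ | Final score | Interaction | ANCOVA | Interaction CI wider than ANCOVA CI by |
|---|---|---|---|---|
| 0.2 | 80% | 60% | 79% | 25% |
| 0.3 | 80% | 66% | 82% | 21% |
| 0.5 | 80% | 80% | 88% | 12% |
| 0.7 | 80% | 95% | 96–97% | 5% |

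The large-sample width ratio √(2/(1 + ρ)) would give 29%, 24%, 15% and 8%. Those figures are too large here because they ignore the cost of the slope. At ρ near 0.9 the gain from adjustment is negligible, and at 0.95 the change-score interval is marginally narrower than the ANCOVA interval (ratio 0.98).

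**Step 5: bias.** In 20,000 simulated trials per value of ρ (0.3, 0.5 and 0.7) with a true effect of −4, the final-score, change and ANCOVA estimates all averaged about −4.0.

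**Step 6: sensitivity to the SD.** At an assumed SD of 5, the final-score test has 43% power. The interaction has 33%, 43% and 64% at ρ = 0.3, 0.5 and 0.7. Baseline adjustment has 46%, 54% and 70%, before the small cost of the slope.

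**The case against.** The strongest reply is that the planned analysis is valid and the article does not commit to the contrast being criticised. A reader might infer that the protocol's treatment effect is a raw difference in change and so contradicts its own sample size calculation. The text does not support that as fact. It names no contrast, and the week-12 contrast of the same model is exactly the final-score comparison that was sized. Leaving the contrast to a statistical analysis plan is ordinary and is not counted here as a fault.

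A reader might also infer bias, or that the baseline is thrown away. Neither follows. All three estimators have the same expectation under randomisation. A change score does use the baseline, with its coefficient fixed at 1, and above ρ = 0.5 it beats the final-score test.

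Nor is adjustment a gain everywhere. Against the final-score contrast it gains nothing at ρ = 0.2 (79% against 80%), and against the interaction it gains almost nothing at ρ near 0.9.

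Finally, the SD, ρ and allocation are assumptions, and the missing SD could matter more than the choice of model. At an SD of 5, all three analyses fall short of 80% at every ρ from 0.3 to 0.7.

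All of this stands, and it limits the point to one of efficiency. It does not remove it. The fixed effects are stated, they include no baseline adjustment, and both natural contrasts are less precise than an adjusted estimate over most of the plausible range of ρ.

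**Conclusion.** The point holds as a loss of efficiency in a method the article has fixed. It is neither an error of validity nor a proven contradiction.

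If the interaction is the test, the loss against baseline adjustment is about 19 power points at ρ = 0.2, 16 at 0.3, 8 at 0.5 and 1 to 2 at 0.7. Its power falls below the sized 80% only when ρ is under 0.5. If the week-12 contrast is the test, power stays at 80%, and adjustment would add about 2 points at ρ = 0.3, 8 at 0.5 and 16 to 17 at 0.7.

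It would be wrong to conclude that the model makes the trial underpowered. That depends on the contrast chosen and on a correlation the article does not give. The figures rest on 11 per arm, a two-sided 5% test, 80% intended power, the back-solved SD of 3.18 and complete data. The change is worth making because it protects precision whichever contrast was intended and whatever ρ proves to be, apart from a trivial cost at the extremes.

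**What to change.** State in Statistical analysis that the primary estimate for the ICIQ-SF score is the between-group difference at 12 weeks, adjusted for baseline ICIQ-SF, with its 95% confidence interval. Either of two models will do:

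- ANCOVA of the 12-week score on group and baseline score.
- The planned mixed model with a common baseline mean: time and group-by-time, without a group main effect. The treatment term should be coded as a single indicator equal to 1 only for group II at 12 weeks. Dropping the group term while keeping a full factor-by-factor interaction merely re-expresses the unconstrained model.

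The sample size section may stay on final scores: under the assumptions above, 22 women give the adjusted analysis about 79% power at ρ = 0.2 and more at higher ρ.

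The cost is a sentence or two of wording. Baseline ICIQ-SF is already collected, and the Trials status section says recruitment has not started. The only statistical price is one degree of freedom for the slope if ANCOVA is used (19 residual degrees of freedom instead of 20).

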## Methods

### Study design

We will conduct an assessor blind randomized, controlled, two-arm clinical trial to assess whether the combination of a low-calorie diet and PFMT will optimize the results obtained with diet therapy as a single intervention to decrease UI prevalence reports and severity in obese women (primary outcome). The secondary outcomes of this study are the impact of the protocol on PFM function, women’s self-perception of their PFM, adherence, and satisfaction with the treatment. This protocol will be reported according to the Protocol Items Standard: Recommendations for Intervention Trials checklist (SPIRIT) 2013: items recommended for a clinical trial protocol and related documents. It is a superiority trial.

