### Inclusion criteria

Women over 18 years, with a body mass index (BMI) > 30 kg/m^2^; reporting stress urinary incontinence, urgent urinary incontinence, or mixed urinary incontinence in the past 4 weeks assessed by the ICIQ-SF; who are able to contract the pelvic floor muscles (assessed using vaginal palpation with a PFM contraction ≥ 2 according to the modified Oxford grading scale); and without any cognitive impairment.

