### Assessment

#### Primary outcome measures

Self-report of urinary incontinence will be measured by question 3 of the ICIQ-SF. Women will be considered incontinent if they choose options 1, 2, 3, 4, or 5 of question 3. Women will be considered continent if they choose option 0 in question 3.

The severity and impact of urinary incontinence on women’s quality of life will be measured by the ICIQ-SF score.

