It seems urgent to conduct high-quality RCTs to investigate the efficacy of associating PFMT with weight loss mediated by diet therapy. The protocol of this RCT was carefully planned following the quality criteria to enhance optimal internal e external validity. Additionally, we will investigate the impact of the intervention on women’s adherence to treatment, on their self-perception of their PFM, and satisfaction with the treatment. Brazilian women’s knowledge about PFM function and dysfunction is low [22, 23]. PFMT protocol must include an education component about PFM function not only to increase women’s knowledge about it but also to improve their adherence to treatment [24, 25]. We will also have the chance to identify barriers and facilitators related adherence to the proposed interventions. A recent study has shown that women with worse PFM function tend to overestimate their PFM function [13]. The self-perception of the PFM function is important for women to localize and to exercise their PFM. Another innovation of this RCT will be to analyze the impact of the intervention with and without PFMT in women’s self-perception of their PFMT and our hypothesis is that more women in the group receiving PFMT in addition to low-calorie diet will improve their PFM perception compared to the group receiving only low-calorie diet.

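### Self-reported incontinence is a named primary outcome of a superiority trial, but the only test named for categorical variables is a before/after McNemar test, and no between-group analysis is specified for it

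*Protocol article*

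**What the plan says.** The Abstract (Methods) states: "The primary outcome of the study is self-reported UI, and severity and impact of UI" is to be assessed by the ICIQ-SF score. Study design puts both the prevalence of reported incontinence and its severity under the primary outcome, and adds: "It is a superiority trial". Primary outcome measures defines the first component as binary: "Self-report of urinary incontinence will be measured by question 3 of the ICIQ-SF", with options 1 to 5 counted as incontinent, and "Women will be considered continent if they choose option 0 in question 3".

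Statistical analysis names two methods. A linear mixed model with group, time and their interaction is assigned to the ICIQ-SF score. Then, as an addition, "the McNemar test will verify changes in categories variables before and after the intervention".

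Three other places bear on the point:
- Inclusion criteria admits women "reporting stress urinary incontinence, urgent urinary incontinence, or mixed urinary incontinence in the past 4 weeks assessed by the ICIQ-SF".
- Intervention gives the same low-calorie diet to both groups.
- Discussion treats the benefit of weight loss on incontinence as established.

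**The concern.** A superiority question about PFMT needs a contrast between women who had it and women who did not. McNemar's test is paired: it asks whether the women it is applied to changed between two time points. Run within an arm, it ignores the other arm. Run on both arms pooled, it ignores allocation altogether.

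Two design features sharpen the problem:
- Entry requires reported incontinence, so the cell for women moving from continent to incontinent is essentially empty. The test reduces to counting how many became continent.
- Both arms receive an intervention that the article expects to improve incontinence, so some conversion to continence is to be expected in both arms even if PFMT adds nothing.

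At stake is the answer on one of the two components of the primary outcome. Followed as written, the text yields a p-value for change over time and none for the effect of PFMT.

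**Working it through.** **Inputs from the article.** Total sample 22 (Sample size calculation); significance level 0.05 (Statistical analysis); all women incontinent at baseline (Inclusion criteria).

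**Assumptions.** 1:1 allocation with no dropout, so 11 per arm; two-sided tests; the exact form of McNemar; true continence rates at 12 weeks of 20% to 60%. The article gives no continence rates.

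**The plan's own figure.** The 22 rests on a 4-point difference in ICIQ-SF score, but no SD is given, so it can be neither confirmed nor refuted. The SD that would give 11 per arm at 80% power is 4 × √(11/2) / (1.960 + 0.842) = 3.35. At the printed power of 20% it is 4 × √(11/2) / (1.960 − 0.842) = 8.39. The point made here does not depend on this SD.

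**Step 1: when McNemar becomes significant.** With one discordant cell empty and c women becoming continent, the exact two-sided p = 2 × 0.5^c.
- c = 5: 2 × 0.03125 = 0.0625
- c = 6: 2 × 0.015625 = 0.031

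So 6 of 11 is the threshold in either arm, whatever happens in the other. The continuity-corrected chi-square has the same threshold: (6 − 1)²/6 = 4.17 exceeds 3.84, while (5 − 1)²/5 = 3.20 does not. The uncorrected chi-square equals c and would already pass at 4.

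**Step 2: two example results.** With 6/11 continent on PFMT plus diet and 5/11 on diet alone, McNemar gives 0.031 and 0.0625, while Fisher's exact test between arms gives p = 1.0. With 6/11 in both arms, McNemar gives 0.031 in each and Fisher again gives 1.0.

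**Step 3: how often this happens when PFMT adds nothing.** Let S = P(X ≥ 6) for X ~ Binomial(11, rate). The chance that the PFMT arm is significant and the diet arm is not is S × (1 − S); at a rate of 40% this is 0.247 × 0.753 = 0.186. The pooled column is P(X ≥ 6) for X ~ Binomial(22, rate), because the text does not say whether McNemar is run by arm or pooled. The Fisher column sums the probability of all 11-versus-11 tables with p ≤ 0.05.

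| True rate, both arms | McNemar significant, PFMT arm | PFMT arm significant, diet arm not | McNemar significant, arms pooled | Fisher between arms significant |
|---|---|---|---|---|
| 20% | 1.2% | 1.2% | 26.7% | 1.0% |
| 30% | 7.8% | 7.2% | 68.7% | 1.4% |
| 40% | 24.7% | 18.6% | 92.8% | 1.6% |
| 50% | 50.0% | 25.0% | 99.2% | 1.7% |
| 60% | 75.3% | 18.6% | 100.0% | 1.6% |

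The McNemar columns follow the shared continence rate; the Fisher column does not.

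**Step 4: what a between-group test can deliver here.** By the same enumeration, Fisher's power with 11 per arm is 17% for an assumed 20% versus 50% continent, and 32% for 20% versus 60%. By the usual two-proportion formula, 80% power would need 78 and 46 women in total (90 and 56 with continuity correction).

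**The case against.** The strongest reply is that this is a condensed article and the comparison may simply be left to a fuller plan. McNemar is introduced as an addition to a model that does contain a group term. The Abstract promises, in general terms, a mixed-effects comparison of the outcomes. The Discussion also thinks between groups when it expects that "more women in the group receiving PFMT in addition to low-calorie diet will improve their PFM perception compared to the group" on diet alone, although that hypothesis concerns PFM perception, not continence. All this shows an intent to compare. It does not supply an analysis: the Abstract names no binary model, and the Methods assign a linear model to the score. The article also does not stay silent on categorical variables; it names a test, and that test cannot answer the trial's question.

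Some stronger readings are tempting but are not supported:
- *The trial has no valid primary comparison.* It has one. Sample size calculation and Table 2 treat the ICIQ-SF score as the primary measure, and that score gets a group-by-time analysis.
- *The investigators will present a within-arm McNemar result as a PFMT effect.* Nothing in the article says so. The percentages show how often the named test would invite that mistake, not that it is planned.
- *Every categorical outcome is misassigned to McNemar.* The yes/no satisfaction items are collected only after the intervention, so a sentence about before/after change does not clearly cover them. Nothing says that MOGS grades will go into the test.
- *The test misleads at any plausible rate.* At a true rate of 20%, the pattern of one significant and one non-significant arm occurs in only about 1% of trials. The Discussion speaks of improvement, not of complete continence, so low rates are possible.

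**Conclusion.** The point holds in this form: for self-reported incontinence on question 3, no between-group analysis is specified, and the one test named for categorical variables cannot estimate what PFMT adds to diet. That follows from the text and does not depend on any assumed rate.

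The size does depend on assumptions. With 11 per arm, no dropout, exact tests and equal true continence rates of 20% to 60%, McNemar in the PFMT arm is significant in about 1% to 75% of trials. The pattern of a significant PFMT arm beside a non-significant diet arm occurs in about 1% to 25%. A between-group Fisher test stays under 2%. The gap is limited to the binary component; the analysis of the ICIQ-SF score is not affected.

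**What to change.** In Statistical analysis, add for question 3 a between-group comparison at 12 weeks by randomised group: the proportion continent in each group, the risk difference with an exact or score 95% confidence interval, and Fisher's exact test. State how women without a 12-week answer are counted. Because all women start incontinent, this comparison at 12 weeks is also the comparison of change. Keep McNemar, if wanted, as a description of change within groups, and say that it is not evidence for PFMT.

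The cost is a change of wording, with no new data or visits. Trials status reports that recruitment had not started, so it can be made before any data exist. The downside should be stated openly: with 22 women the comparison has little power (17% to 32% under the two scenarios above), so it should be reported mainly as an estimate with its interval, and a non-significant result should not be read as absence of effect. The sponsor may also consider making question 3 secondary to the ICIQ-SF score, on which the sample size rests.
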